**Comments:**

**Protocol, UNICIRC clinical trial 004**  
**Follow-Up Visit: Genital Exam and Wound Healing**

|         |                                                                                                        |                                                                                                      |                                                                                                                                                                                                                                                                                                                                                                                                                                                                                                                                                                                                                                                                                                                                                                                                                                                                                                                        |
|---------|--------------------------------------------------------------------------------------------------------|------------------------------------------------------------------------------------------------------|------------------------------------------------------------------------------------------------------------------------------------------------------------------------------------------------------------------------------------------------------------------------------------------------------------------------------------------------------------------------------------------------------------------------------------------------------------------------------------------------------------------------------------------------------------------------------------------------------------------------------------------------------------------------------------------------------------------------------------------------------------------------------------------------------------------------------------------------------------------------------------------------------------------------|
| Center: | Participant Number:

 | Study Staff Name:

 | Date of Visit:

 

 

 

 

 

 

 

 

 
 
 Day Month Year 
 |
|---------|--------------------------------------------------------------------------------------------------------|------------------------------------------------------------------------------------------------------|------------------------------------------------------------------------------------------------------------------------------------------------------------------------------------------------------------------------------------------------------------------------------------------------------------------------------------------------------------------------------------------------------------------------------------------------------------------------------------------------------------------------------------------------------------------------------------------------------------------------------------------------------------------------------------------------------------------------------------------------------------------------------------------------------------------------------------------------------------------------------------------------------------------------|

4 weeks, and optional 6 week follow-up visit

1. Is this a scheduled visit?.....   
0 = No  
1 = Yes  
**1a. If NO, what is the reason for this unscheduled visit?** \_\_\_\_\_  
\_\_\_\_\_

2. What is the post-op day?  
.....  
e.g. 28 = Day 28 42 =(optional) Day 42

**GENITAL EXAM**

3. Aside from the circumcision wound, are the genitals normal? .....   
0 = No  
1 = Yes  
**3a. If NO, describe:** \_\_\_\_\_  
\_\_\_\_\_

**WOUND HEALING**

5. Did the participant have any difficulty keeping the wound clean and dry? .....   
0 = No  
1 = Yes  
**5a. If YES, describe:** \_\_\_\_\_  
\_\_\_\_\_

6. Has the wound completely healed (no wound, completely epithelialized)? .....   
0 = No  
1 = Yes → **SKIP REST OF QUESTIONS**

7. Is there wound disruption or dehiscence?.....   
0 = None    1 = < 2cm  
2 = More than 2 cm

8. Is there any swelling?.....   
0 = None    2 = Moderate  
1 = Mild    3 = Severe (if severe, complete AE form)

For Questions 9-13, if response is "moderate" or "severe," complete AE form and take a photo with participant's permission.

9. Is there any evidence of infection?.....   
0 = None    2 = Moderate  
1 = Mild    3 = Severe

10. Is there any bleeding?.....   
0 = None    2 = Moderate  
1 = Mild    3 = Severe

11. Is there a hematoma?.....   
0 = None    2 = Moderate  
1 = Mild    3 = Severe

12. Does the participant report difficulty or pain with urination? .....   
0 = None    2 = Moderate  
1 = Mild    3 = Severe

13. Are there any other complications?.....   
0 = None    2 = Moderate  
1 = Mild    3 = Severe

**13a. If response is 1, 2, or 3, describe complication:** \_\_\_\_\_  
\_\_\_\_\_

14. Was any medication given to or prescribed for the participant at this visit?.....  
0 = No  
1 = Yes → **LIST MEDICATIONS**  
\_\_\_\_\_  
\_\_\_\_\_

15. Final Cosmetic Result .....  
1= Regular  
2= Irregular  
3 =Scalloped (wavy)

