*Secondary outcomes:* Complications (operative and post-operative); time to healing; direct costs; post-operative pain; patient satisfaction; cosmetic result.

Protocol, UNICIRC clinical trial 004

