**4 weeks, and optional 6 week follow-up visit**

**CIRCUMCISION ACCEPTABILITY**

**15. How satisfied are you with the appearance of your circumcision?**.....|\_|

- 1 = Very satisfied →  
 2 = Somewhat satisfied →  
 3 = Somewhat dissatisfied  
 4 = Very dissatisfied

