**17. What did you like about the circumcision?**

**18. What did you NOT like about the circumcision or what improvements would you suggest?**

**19. If the participant is either (1) newly identified as being completely healed at this visit, or (2) has an adverse event or is dissatisfied, does the participant permit us to take a picture of his penis?**.....|\_|

- 0 = No  
 1 = Yes (take a picture of penis)

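### On the 4-week form a healed wound routes staff past the only cosmetic rating, so this secondary outcome would be scored only in unhealed men

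*Protocol*

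**What the plan says.** The Protocol Summary lists six secondary outcomes: "Complications (operative and post-operative); time to healing; direct costs; post-operative pain; patient satisfaction; cosmetic result". It also says that the study will show Unicirc to heal faster and to look good, and it offers the 42-day visit only to men who are not fully healed at 4 weeks.

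The form for the 4-week and optional 6-week visit asks, in its Wound Healing section, "Has the wound completely healed (no wound, completely epithelialized" (item 6). Beside the answer Yes stands "SKIP REST OF QUESTIONS". The instruction names no item or page at which the skip ends.

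After it, in the same section, come items 7 to 13 on dehiscence, swelling, infection, bleeding, haematoma, urination and other complications, then item 14 on medication, and last "15. Final Cosmetic Result", scored regular, irregular or scalloped.

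The next page has a new participant header and the heading Circumcision Acceptability. Its first question, also numbered 15, is "How satisfied are you with the appearance of your circumcision". Item 19 on that page asks permission for a photograph if the man is "newly identified as being completely healed at this visit", has an adverse event or is dissatisfied.

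**The concern.** A cosmetic rating called final should describe the healed result. The routing does the reverse: a man whose wound has healed is sent past the item, and a man whose wound is still open is rated. Whether a value exists then depends on healing, which is itself a secondary outcome and is observed after randomisation. The sponsor expects healing to be faster in one arm, so the rated subsets of the two arms would be selected to different degrees. A comparison of those subsets does not estimate the difference between the randomised groups. No healed man would contribute a rating from which the missing ones could be modelled.

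Two further effects follow from the same line. Healed men are not prompted at this visit for problems that complete epithelialisation does not rule out. The skip also collides with an acceptability item written for healed men, so two staff members could collect satisfaction from different sets of participants.

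**Working it through.** The plan gives no figure for this point, so there is none to reproduce. The check traces the routing and then illustrates its size.

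**Routing, item by item**

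1. *Is the cosmetic result recorded anywhere else?* The surgical report, the 7-day form and the unscheduled-visit form contain no cosmetic rating. The 4/6-week form is the only place shown.
2. *Man healed at day 28.* Item 6 is Yes, so the cosmetic item is skipped. The 42-day visit is not meant for him. He is never rated.
3. *Man unhealed at day 28, healed at day 42.* He is rated at day 28 with the wound unhealed, and skipped at day 42. His only rating predates healing.
4. *Man unhealed at both visits.* He is rated at both, unhealed each time.
5. *Result.* Under a literal reading, no rating comes from a healed wound, and the men with a rating are those unhealed at day 28.

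**Complications.** Items 7 to 14 are skipped in healed men at this visit. Dehiscence (item 7) is largely moot once the wound has closed. Swelling (item 8), difficulty urinating (item 12), other complications up to "13. Are there any other complications" and medication (item 14) are not. Operative complications are on the surgical report, the 7-day form asks every man with no healed skip, and the adverse-event and unscheduled-visit forms do not depend on healing.

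**Satisfaction.** A literal skip omits the acceptability page. Item 19 on that page presupposes that newly healed men reach it. Both cannot be followed.

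**Illustration of the share missing.** Arm sizes, from the Summary: 50 Unicirc and 25 open surgery. The proportions healed at day 28, pU and pO, are assumptions.

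Men rated = 50 × (1 − pU) and 25 × (1 − pO). Share missing = (50 × pU + 25 × pO) / 75.

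| Assumed healed, Unicirc / open | Rated, Unicirc | Rated, open | Missing of 75 |
|---|---|---|---|
| 60% / 40% | 20 | 15 | 40 / 75 = 53% |
| 80% / 50% | 10 | 12.5 | 52.5 / 75 = 70% |
| 95% / 80% | 2.5 | 5 | 67.5 / 75 = 90% |

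**Illustration of the bias.** Assume a regular result in 95% of healed and 60% of unhealed men in both arms, with 90% (Unicirc) and 70% (open) healed at day 28.

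- All men, Unicirc: 0.90 × 95% + 0.10 × 60% = 91.5%.
- All men, open: 0.70 × 95% + 0.30 × 60% = 84.5%.
- True difference: 7 percentage points.
- Recorded data, unhealed men only: 60% against 60%, a difference of zero.

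Under these assumptions, the routing would hide a real advantage of the sponsor's own device.

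**The case against.** The strongest reply is that this is a routing slip that staff would see through. An item labelled final is plainly meant for the end result, and the skip may have been intended only for the wound-problem items. That is plausible, but the form does not say so, and data for a named outcome should not depend on staff departing from a written instruction.

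Three stronger readings are tempting, and the documents do not support them.

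- *Satisfaction is lost in all healed men.* The acceptability questions have their own page and heading, and item 19 expects healed men there. What stands is a contradiction with an uncertain result, not a sure loss.
- *Complications are recorded only in unhealed men.* The surgical, 7-day, adverse-event and unscheduled-visit forms record them regardless of healing, and the genital examination on the 4/6-week form precedes the skip. Only that form's later prompts are lost.
- *The cosmetic data are beyond any rescue.* Photographs of newly healed men might support a later rating. But they need permission, lie on the page that a literal skip omits, and come with no stated grading procedure. They are a partial fallback.

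It is also fair that the percentages above rest on assumed healing rates and full compliance with the skip, and that the difference by arm rests on a qualitative expectation in the Summary. This limits the size that can be claimed but leaves the routing fault as it is. Nor can the analysis plan settle the matter, since an analysis plan cannot supply ratings that were never taken.

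**Conclusion.** The point holds in this form: item 6 has a skip with no end point. Followed as written, it removes the cosmetic result, one of six named secondary outcomes, in every healed man, and leaves ratings only from unhealed wounds. The missingness depends on a post-randomisation outcome that the protocol expects to differ by arm. The skip also drops the later complication and medication prompts in healed men at the 4/6-week visits, and it leaves unclear whether their satisfaction is collected.

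The share missing cannot be estimated from the documents. The range of 53% to 90% of 75 men holds only for assumed healed proportions of 60%/40% to 95%/80% and literal compliance. The conclusion about the cosmetic item also rests on its absence from every other form shown. Intraoperative time, the primary outcome, is taken from the surgical report and is unaffected.

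**What to change.** Rewrite the routing at item 6 so that a Yes skips only the dehiscence item (item 7). State that items 8 to 14, the cosmetic rating and the whole acceptability page are completed for every man in both arms. This also removes the conflict with item 19.

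Score the cosmetic result at the 4-week visit in all men, healed or not, and repeat it at 6 weeks in those who return. A common 4-week rating keeps the time of assessment independent of healing speed. Rating each man at the visit where he is first found healed would bring that dependence back.

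The cost is a one-line form correction and a few minutes per visit. It needs to be in place before the first 4-week visit, because a rating not taken then cannot be recovered reliably.

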**SUMMARY**

According to the Framework for Clinical Evaluation of Devices for Adult Male Circumcision (WHO, 2011): *“WHO and other health authorities wish to identify one or more devices that (a) would make the VMMC safer, easier, and quicker; (b) would have more rapid healing than current methods and/or might entail less risk of HIV transmission in the post-operative period; (c) could be performed safely by health-care providers with a minimal level of training; and (d) would be cost-effective compared to standard surgical methods for male circumcision scale up.”*

Because of difficulties and small risks entailed in using sterilizable instruments, WHO prefers disposable, single-use-only instruments be used for circumcision. This proposed randomized controlled trial will provide important data which will inform and enable the South African health system to more effectively scale-up circumcision services. This study will prove that VMMC using the Unicirc disposable single-use-only instrument coupled with tissue adhesive meets WHO criteria for the ideal method: it is faster, easier to learn, safer for both surgeons and patients, heals sooner, has excellent cosmetic results, and is more cost effective than any other currently available technique.

We propose a randomized controlled trial (RCT) comparing this minimally-invasive circumcision technique to the open surgical technique. In accordance with WHO recommendations concerning sample size found in the Framework for Clinical Evaluation of Devices for Adult Male Circumcision, we propose to study:

- Unicirc disposable instrument with topical anaesthetic and tissue adhesive wound sealing: 50 men
- Open surgical circumcision: 25 men

This is the fourth study of Unicirc circumcision, and the second study that uses topical anaesthetic instead of injectable local anaesthetic. Tissue adhesive is widely used in multiple areas of medicine; specifically, multiple observational studies and RCTs have shown cyanoacrylate tissue adhesives to be superior to suture closure in VMMC. The open surgical method will serve as the control intervention.

*Population:* Men at least 18 years of age who desire male circumcision

*Study design:* Randomized controlled trial

*Intervention:* Unicirc instrument circumcision plus tissue adhesive vs. open surgical circumcision

*Follow-up visits:* 7 days and 28 days. Optional 42 day follow-up if not completely healed by 4 weeks.

*Primary outcome:* Intraoperative time

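### No masked or independent assessor is specified for complete healing or final cosmetic result, and the planned photographs depend on the on-site healing call

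*Protocol*

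**What the plan says.** The Summary describes the design as follows: "We propose a randomized controlled trial (RCT) comparing this minimally-invasive circumcision technique to the open surgical technique". It allocates 50 men to Unicirc and 25 to open surgery, names intraoperative time as primary, and lists time to healing and cosmetic result among the secondary outcomes. It also says in advance what the study is going to prove, including that the method "heals sooner, has excellent cosmetic results".

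The two outcomes are captured on the 4-week and optional 6-week form, under Wound Healing:

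- Item 6: "Has the wound completely healed (no wound, completely epithelialized", answered yes or no. A yes carries an instruction to skip the remaining questions.
- "15. Final Cosmetic Result": regular, irregular or scalloped, with no scoring rule. It is the last item of that section, so it comes after the skip.

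The form has a field for the study staff member's name, and the Surgical Report Form has fields for the first and second surgeon. Nothing says these must be different people. Masking is not mentioned anywhere in the protocol shown.

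Photographs, always with permission, are taken in two situations. Items 9–13 call for one when a finding is moderate or severe. Item 19 asks for one when a man is "newly identified as being completely healed at this visit", has an adverse event or is dissatisfied.

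**The concern.** Whether a wound is fully epithelialized and whether a scar line is regular are visual judgements at a threshold. If the person judging knows the technique, or performed it, and works under a protocol that already states the expected answer, borderline cases can drift towards the device. That is detection bias, and no later analysis can remove it if no independent rating was collected. Who assesses an outcome is a design matter for the protocol, not one normally left to the SAP.

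The photographs do not close the gap as planned. The item 19 request is triggered by the same on-site call that would need checking. A masked reader could therefore overturn a healed call, but could rarely overturn a not-healed call.

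The skip adds a recording problem. Read literally, a man called healed at item 6 never receives a cosmetic rating, although healed men are those for whom a final cosmetic result means most.

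**Working it through.** **What the protocol gives.** Arm sizes: "Unicirc disposable instrument with topical anaesthetic and tissue adhesive wound sealing: 50 men" and "Open surgical circumcision: 25 men", so 75 in total at 2:1. The size is attributed to a WHO framework. No alpha, power, healing rate or effect is stated, so there is no planned figure to reproduce. Every rate below is an assumption.

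**Step 1. Effect of differential rating on the healing comparison.** Assume 70% truly healed at day 28 in both arms. If a fraction f of unhealed Unicirc men are called healed, the observed Unicirc rate is 0.70 + 0.30f:

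- f = 1/6: 0.70 + 0.05 = 0.75
- f = 1/3: 0.70 + 0.10 = 0.80

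The rejection probability is the sum, over all outcomes (a of 50, b of 25) where a two-sided 5% test rejects, of Bin(a; 50, p1) × Bin(b; 25, p2). The protocol names no test, so two are shown.

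| Observed rates, Unicirc v open | Pooled z at 1.96 | Fisher's exact |
|---|---|---|
| 70% v 70% (no shift) | 0.051 | 0.035 |
| 75% v 70% (5 points) | 0.081 | 0.053 |
| 80% v 70% (10 points) | 0.171 | 0.125 |
| 80% v 60% (shifts in both arms) | 0.462 | 0.376 |

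In the 10-point case nearly all rejections favour Unicirc (0.169 of 0.171 by z). The last row needs open-surgery men to be under-called by 10 points as well.

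**Step 2. A second bias model.** Let an unhealed Unicirc man be called healed with probability m, and a healed open-surgery man be called unhealed with probability m/2. Over true healing rates of 50–90%, Fisher's test favours Unicirc 6–9% of the time for m = 0.1, 17–23% for m = 0.2 and 35–45% for m = 0.3, against about 2% for m = 0.

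**Step 3. Who would have a photograph at day 28.** Let h be the share called healed, q the share of the unhealed with an adverse event or dissatisfaction, and c the permission rate.

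- Men photographed = 75 × c × [h + (1 − h)q]
- Men called unhealed and not photographed = 75 × (1 − h) × (1 − qc)

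With h = 0.7, q = 0.1 and c = 0.9:

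- 75 × 0.9 × (0.7 + 0.03) = 49.3 men photographed
- 75 × 0.3 × (1 − 0.09) = 20.5 of 22.5 unhealed men without an image

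With q from 0 to 0.2 and c from 0.7 to 1.0, the unhealed men without an image number 30–37.5 of 37.5 if h = 0.5, and 6–7.5 of 7.5 if h = 0.9. Most unhealed men lack an image throughout this range.

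**Step 4. The skip.** Item 6 comes before the cosmetic item in the same section, so a yes bypasses it. The skip cannot be meant to run to the end of the form, because item 19 expressly applies to newly healed men. Its intended end is not stated.

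**The case against.** A reader might infer that staff who know the arm do the rating. The protocol does not say so: it is silent on who completes items 6 and 15 and on what that person knows. Separate name fields for surgeon and visit staff show neither that they are the same person nor that they differ. What stands is that no masking is specified and nothing bars the surgeon.

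A reader might also infer that the photographs needed for masked scoring are already planned. That is true at most for cosmesis, subject to permission; step 3 shows why it fails for healing. Widening item 19 is therefore a new request to some men, not a reuse of existing images.

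The word subjective can be pressed too far. Item 6 has a stated criterion, and men rate their own satisfaction with appearance on four levels, so appearance does not rest on staff scores alone. But applying the criterion remains a judgement, and participant satisfaction is a separate listed outcome that says nothing about healing.

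Masking from images is imperfect, since adhesive and open surgery may leave different marks, and a still image may show epithelialization less well than live examination. Replacing the live healing call with an image code would also mix two measurement methods, with the mix set by who gives permission. This stands, and is why the live examination should remain the healing outcome.

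Finally, the rates and shifts in steps 1 and 2 are hypothetical. This stands too: they show what differential rating could do, not that it will occur, and they say nothing about cosmesis.

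**Conclusion.** The point holds in a limited form. Two judgement-based secondary outcomes have no masked or independent assessor specified, the operating surgeon is not excluded, and the conclusion is stated in advance. The conditional photographs could serve masked cosmetic coding but not masked healing scores.

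Under an assumed 70% healed at day 28 in both arms, a 10-point rating shift would produce a significant difference about 13–17% of the time and a 5-point shift 5–8%, depending on the test. The 38–46% figure requires opposite errors in the two arms against a stated criterion and should not be read as an expected error rate.

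The primary outcome, intraoperative time, and the sample size lie outside this point. It is a worthwhile improvement rather than a flaw that threatens the trial. The skip ahead of the cosmetic item is a separate, concrete form error at the same place.

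**What to change.** 1. State that the follow-up examiner is not a surgeon named on that man's Surgical Report Form.
2. Widen item 19 to request a standard photograph from every consenting man at day 28, and at day 42 if he attends, whatever the healing call.
3. Have existing study staff who did not operate on that man code the images, labelled by participant number only. Keep the live examination as the healing outcome. Use the image code as a check on healing and as the masked cosmetic rating.
4. Move the final cosmetic result outside the item 6 skip, so that it is recorded for healed men, and state where the skip ends.

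Cost: one sentence, two form edits and the coding of up to 75 day-28 images plus any from day 42. No added staff are needed, provided the team includes someone who did not operate on the man concerned; the protocol does not give staffing. Masking will be partial where the technique leaves visible marks, and some men will refuse a photograph, so the number of men without an image should be reported by arm.
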